## Inclusion Criteria

Those eligible for enrolling are type 2 diabetes patients aged 18 years or older, who have been diagnosed and followed up for type 2 diabetes for at least six months, have an HbA1c greater than 8% at the time of enrolment, and only one family member from each household will participate in the study. Furthermore, they should be able to understand Malay and have internet access at home.

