## Data collection method

Data will be collected by the research by selecting type 2 diabetes patients from the baseline. These type 2 diabetes patients will have to meet the inclusion and exclusion criteria, once it is fulfilled the type 2 diabetes patients will be recruited. A research assistant will approach patients on the day of their follow-up visit at Klinik Kesihatan Cheras Baru. As part of the consent process, the investigator will explain and provide the Patient Information Sheet to the participant and an agreement to receive calls and messages from the researcher for research purposes. They will keep their phone numbers private and will only be contacted or messaged every four weeks to remind them to complete the videos watching and follow-up appointment. The patients will, however, be given one week to consider their participation if they are still deciding on the recruitment day. We will conduct a one-to-one ratio randomization control trial with the control and intervention groups.

During the same day, all participants will be given a hard copy self-administered questionnaire by research assistance to complete and their latest clinical profile (height, weight, BMI, waist circumference, blood pressure, latest blood test for HbA1c and fasting lipid profiles) will be taken from their medical records. The self-administered questionnaire will take about 20minutes to complete. This stage will be considered as baseline assessment for both control and intervention groups. After the questionnaire, both groups will continue their follow up in the clinic like usual. The intervention group will take place after all the participants complete the questionnaire. The participants will be told about the structure of the program. There will be a research assistant who the researcher has already trained to assist and teach the participants how to assess and use the web-based online education videos. They will need to watch all the videos. The research assistant will follow up with their progress and remind them to complete the video in every four weeks via phone call.

After three months of the intervention on the first week of September (2/9/2024 to 6/9/2024), both of the intervention and control group participants will return to the clinics for follow up. During the follow-up, participants will be given a self-administered questionnaire to answer.

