At six months’ time point from the baseline on the last week of December (23/12/2024 to 31/12/2024), both of the intervention and control group participants will return to the clinics for follow up. During the follow-up, participants will be given a self-administered questionnaire to answer and their latest clinical profile (height, weight, BMI, waist circumference, blood pressure, latest blood test for HbA1c and fasting lipid profiles) will be taken from their medical records. This is a basic diabetes education video for self-care and education, and no further treatment will be given after the study has been completed. You will continue your diabetes follow up as usual.

*Figure 2: Flow of the process*

[figure not shown]

Collection of questionnaires port write up and dissemination of result

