## Operational Definition

| **DEPENDANT VARIABLE** | **DEFINITION** |
| --- | --- |
| Diabetes knowledge | Self-reported by participant their diabetes knowledge |
| *HbA1c* | HbA1c level as measured the latest, and obtained by checking  patient’s record |
| *Blood pressure* | Blood pressure as measured most recently |
| *Fasting lipid profile* | Include HDL, LDL and TG level as measured the latest and  obtained by checking patient’s record |
| *Body Mass Index (BMI)* | BMI is calculated as the weight in kg divided by meter square  and classify according to WHO (for Asian population)  Underweight: <18.5kb/m2  Normal: 18.5 to 22.9kg/m2  Overweight: 23 to 27.49kg/m2  Obese: 27.5 to 30kg/m2  Obese II: 30 to 35kg/m2  Obese III: 35kg/m2 and above |
| *Waist circumference*  *(WC)* | Waist circumference is measure at the midpoint between the  lowest palpable rib and the top of the iliac crest. Normal waist  circumference for male is 90cm and female is 80cm. |
| **INDEPENDENT VARIABLE** | **DEFINITION** |
| **Sociodemographic profile** | |
| Age | Self-reported in years, determined from years of birth |
| Gender | As self-reported by participants |
| Ethnicity | As self-reported by participants |
| Education level | As self-reported by participants the highest education received |
| Marital status | As self-reported by participants single, married, divorce, widow. |
| Employment status | As self-reported by participants their occupation |
| Income | As self-reported by participants, will be grouped as B40, M40  and T20.  B40: RM0 – RM4849  M40: RM4850 – RM10,959 T20:  More than RM10,960 |
| Smoking status | As self-reported by participants smoker, non-smoker or exsmoker.  A smoker is considered to have been successfully quit  smoking if he has been abstinent without even a single puff of  cigarette for at least 6 months from the last cigarette (Quit date) |
| History of hospitalization  due to complication of  type 2 diabetes | As self-reported by participants their past medical history of  hospitalisation due to complication of type 2 diabetes  (Nephropathy, retinopathy, cardiovascular event and diabetes  foot ulcer or amputation) |

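### Six-month HbA1c and lipids are the latest value on record with no date limit, so a pre-randomisation result can be analysed as an observed zero change (secondary outcomes only)

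*Protocol*

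**What the plan says.** Protocol 3.9 (Data collection method) takes the baseline clinical profile from what the chart already holds on the recruitment day ("their latest clinical profile (height, weight, BMI, waist circumference, blood pressure, latest blood test for HbA1c and fasting lipid profiles) will be taken from their", where the sentence goes on to name the chart as the source). For the final assessment it gives the visit dates, "At six months’ time point from the baseline on the last week of December (23/12/2024 to 31/12/2024", and then repeats the rule: "latest blood test for HbA1c and fasting lipid profiles) will be taken from their medical records". The schedule table in 3.20 says the same for both time points and shows no clinical profile at three months.

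Protocol 3.11 (Operational Definition) makes this the definition of the endpoint: "HbA1c level as measured the latest" for HbA1c, a matching entry for lipids, and "Blood pressure as measured most recently" for blood pressure.

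Between the two assessments, "both groups will continue their follow up in the clinic like usual". Sections 3.12 and 3.20 class the clinical measures as secondary. Section 3.12 plans an intention-to-treat analysis with paired t tests and GEE.

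**The concern.** The December dates fix when the participant returns and fills in the questionnaire. They do not fix when the blood test was taken. Nothing in the protocol sets an earliest date for a six-month value, requires it to differ from the baseline value, or says that the absence of a new test counts as missing. Nor does it ask for the date of each value to be recorded.

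Applied exactly, the rule therefore turns a missing six-month result into an observed change of zero. It can also label a result from early follow-up, after little exposure to the videos, as six months. Section 3.2 makes this more likely, because it draws patients from registrations running from 1 June to 31 December 2024 while the final visit stays fixed in late December. Anyone enrolled well after June has less time in which a new test could occur.

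Clinical outcome is one of only two research questions in 1.2. As the rule stands, a null HbA1c result could not be told apart from participants simply not having been retested.

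**Working it through.** **1. The plan's own figure.** Section 3.6 gives changes in knowledge of 0.7 ± 2.21 and -0.30 ± 2.33, 80% power, 5% error and 30% attrition.
- Difference: 0.7 - (-0.30) = 1.0.
- Pooled variance: (2.21² + 2.33²)/2 = 5.157, so SD = 2.271.
- n per group = 2 × (1.960 + 0.842)² × 5.157 / 1.0² = 80.9, rounded up to 81.
- With attrition: 81/0.70 = 115.7, rounded up to 116.

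The stated 116 per group (232 in total) is reproduced. It rests on the knowledge score alone, so the rule for record values does not touch it.

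**2. What the rule does to the mean change.** Let f be the share of participants whose six-month value is their baseline value again, with f unrelated to their true change. Let μ and σ be the mean and SD of true change in an arm. A stale participant has a recorded change of 0, so the arm mean becomes (1-f)μ. With the same f in both arms, the between-arm difference is (1-f) times the true one: 0.90, 0.75 and 0.50 for f = 0.10, 0.25 and 0.50.

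**3. What it does to the variance of change.** Mixing exact zeros with true changes gives

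Var = (1-f)σ² + f(1-f)μ².

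When μ is small relative to σ this is about (1-f)σ². The sample size for equal power is proportional to variance divided by the squared difference, so it rises by about (1-f)/(1-f)² = 1/(1-f). If the SD is instead unchanged, roughly a comparison of six-month values alone, the factor is 1/(1-f)².

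**4. Results.** Power is for a clinical outcome that would have 80% power with no stale values, two-sided 5%. It is Φ(2.802 × √(1-f) - 1.960) for change scores and Φ(2.802 × (1-f) - 1.960) with the SD unchanged.

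| f (assumed) | Effect kept | n factor, change scores | n factor, SD unchanged | Power, change scores | Power, SD unchanged |
|---|---|---|---|---|---|
| 0.10 | 0.90 | 1.11 | 1.23 | 76% | 71% |
| 0.25 | 0.75 | 1.33 | 1.78 | 68% | 56% |
| 0.50 | 0.50 | 2.0 | 4.0 | 51% | 29% |

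**5. Unequal stale shares.** With shares f₁ (intervention) and f₀ (control), the expected difference is (1-f₁)μ₁ - (1-f₀)μ₀. If the intervention does nothing, so that μ₁ = μ₀ = μ, this equals (f₀ - f₁)μ. Participants enter because they "have an HbA1c greater than 8% at the time of enrolment", so HbA1c may fall in both arms by regression to the mean and μ may be negative. A larger stale share among controls would then create an apparent benefit of the videos; a larger share in the intervention arm would create an apparent harm.

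**The case against.** **Only secondary outcomes are affected.** This stands. Knowledge and empowerment come from questionnaires completed at the visits.

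**Blood pressure and weight are probably remeasured in December.** This largely stands. Both arms attend the clinic that week, and the most recent blood pressure may well be that day's reading, although the text does not require it. The real exposure is HbA1c and lipids.

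**The size is unknown.** This also stands. Participants remain in usual care and return twice, so many may be retested. No testing frequency is given, and nothing in the protocol supports a share as high as 0.50.

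A reader might infer several stronger points that the document does not support:
- *The effect must shrink toward zero.* That holds only if the stale shares are similar in both arms.
- *The four-weekly contacts will produce more tests in the intervention arm.* Section 3.9 first describes such contact for participants generally, covering the follow-up appointment as well as the videos, and both arms have the same return visits. Differential testing is possible but not shown.
- *Patients may be enrolled on an old HbA1c.* The inclusion criterion refers to the time of enrolment, and the undated definition in 3.11 is listed under dependent variables. The two should be tied together, but the criterion itself does not admit an old result.
- *The required sample size rises by 1/(1-f)² in every analysis.* That assumes an unchanged SD. Exact zero changes also reduce the variance of change.

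It could also be said that a date window belongs in the statistical analysis plan. Here, however, the protocol itself fixes the endpoint by a stated rule and asks for no dates, so a later plan may lack what it needs to repair it.

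**Conclusion.** The point holds for the secondary clinical outcomes, chiefly HbA1c and fasting lipids. The stated rule can enter a pre-randomisation result as an observed six-month value, or an early one as a late one.

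The loss is the factor (1-f) on the between-arm difference. The matching rise in sample size lies between about 1/(1-f) and 1/(1-f)². This assumes equal stale shares in the two arms, staleness unrelated to true change and, for the lower figure, a mean change that is small relative to its SD. The values of f are illustrative. With unequal shares the direction of bias is not determined.

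The primary questionnaire outcomes and the 116 per group are not in question. The flaw should be fixed, but it does not undermine the main comparison.

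**What to change.** In 3.9, 3.11 and the schedule table in 3.20, replace the latest-value rule with a dated one:
- The six-month value must post-date randomisation and fall in a stated window ending at the 23-31 December visit, for example the six weeks before it. A window centred on six months after randomisation would not fit, because the visit dates are fixed and 3.8 ends data collection on 31 December 2024.
- The baseline value must fall in a stated window before randomisation.
- The date of every clinical value is recorded.
- A value outside its window is set to missing and is not carried in.

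The cost is a short change to the wording in three places and one date field per value. No extra tests are needed. The downside is more missing clinical values, which the analysis must then handle. Those values are already missing in substance; the current rule hides them.

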## Study Instrument

Self-administered questionnaire which will be distributed to respondent in Malay language upon initiation of recruitment as the baseline. This questionnaire will be divided into following sections.

**Section A for sociodemographic factors**

Section A will elicit on socio-demographic factors, such as age, gender, ethnicity, education level, marital status, employment status, income, smoking status, history of hospitalization due to complication of type 2 diabetes.

**Section B for Diabetes knowledge test questionnaire**

Section B will assess general knowledge of diabetes. Validity and reliability of study instrument the translated Malay version Diabetes knowledge test will be used for pre and post-test. For the translated questionnaire, the Cronbach's alpha was acceptable (α=0.573) with the Cronbach’s alpha excluding each item ranged from 0.517 to 0.602. Factor analysis with Varimax rotation identified 6 domains for the 18 items, with 2 to 6 items in each domain.

The score will be calculated in mean.

**Section C for Diabetes empowerment score questionnaire**

Section C will assess general knowledge of diabetes and diabetes self-care. The translated Malay version Diabetes empowerment score test will be used for pre and post-test. For the translated questionnaire, the Cronbach's alpha was acceptable (α=0.760).

A series of web-based education videos will be developed by primary care physicians, dietitian, physiotherapist, occupational therapist, and dentist in English scripts then translated into Malay, Chinese and Tamil.

Expert panellists will edit and review all the web-based educational videos and validate them using a video validation questionnaire with input from endocrinologists, primary care physicians, dietitians, physiotherapists, and occupational therapists and a few patients.

These videos discuss the following topics:

1. Definition and importance of HbA1c.
2. Complications of diabetes.
3. Instructions on self-monitoring blood glucose and the target value.
4. Diabetic medications and side effects.
5. The hypoglycaemia information
6. Diet information pertaining to healthy plates, regular meals, portion sizes, and mindful eating
7. To perform self-foot examination at home.
8. Instruction in home exercise
9. An introduction to eye examinations in diabetes and the need to monitor.
10. The importance of an annual dental check to prevent periodontitis.

Afterwards, the videos will be recorded in Malay, Chinese, Tamil and English with subtitles by the recording by the primary care team. Each video will be about 3 minutes. The technical team will edit the recording.

We will evaluate the feasibility of the videos (clarity of contents and language) with 10 participants. These participants would be type 2 diabetes patients with diverse age groups, ethnicity, and education levels. Their review and feedback will be revised in the videos, if necessary. Once the videos are finalised, they will be uploaded to the social media (e.g TikTok) private account or website for participants to access.

## Operational Definition

| **DEPENDANT VARIABLE** | **DEFINITION** |
| --- | --- |
| Diabetes knowledge | Self-reported by participant their diabetes knowledge |
| *HbA1c* | HbA1c level as measured the latest, and obtained by checking  patient’s record |
| *Blood pressure* | Blood pressure as measured most recently |
| *Fasting lipid profile* | Include HDL, LDL and TG level as measured the latest and  obtained by checking patient’s record |
| *Body Mass Index (BMI)* | BMI is calculated as the weight in kg divided by meter square  and classify according to WHO (for Asian population)  Underweight: <18.5kb/m2  Normal: 18.5 to 22.9kg/m2  Overweight: 23 to 27.49kg/m2  Obese: 27.5 to 30kg/m2  Obese II: 30 to 35kg/m2  Obese III: 35kg/m2 and above |
| *Waist circumference*  *(WC)* | Waist circumference is measure at the midpoint between the  lowest palpable rib and the top of the iliac crest. Normal waist  circumference for male is 90cm and female is 80cm. |
| **INDEPENDENT VARIABLE** | **DEFINITION** |
| **Sociodemographic profile** | |
| Age | Self-reported in years, determined from years of birth |
| Gender | As self-reported by participants |
| Ethnicity | As self-reported by participants |
| Education level | As self-reported by participants the highest education received |
| Marital status | As self-reported by participants single, married, divorce, widow. |
| Employment status | As self-reported by participants their occupation |
| Income | As self-reported by participants, will be grouped as B40, M40  and T20.  B40: RM0 – RM4849  M40: RM4850 – RM10,959 T20:  More than RM10,960 |
| Smoking status | As self-reported by participants smoker, non-smoker or exsmoker.  A smoker is considered to have been successfully quit  smoking if he has been abstinent without even a single puff of  cigarette for at least 6 months from the last cigarette (Quit date) |
| History of hospitalization  due to complication of  type 2 diabetes | As self-reported by participants their past medical history of  hospitalisation due to complication of type 2 diabetes  (Nephropathy, retinopathy, cardiovascular event and diabetes  foot ulcer or amputation) |

## Statistical Analysis Plan

#### Dependent Variables

In this study, the primary outcome of interest is diabetes knowledge and the secondary outcome is clinical outcome (HbA1c, blood pressure, fasting lipid profile, BMI, waist circumference) among intervention and control groups at baseline.

#### Independent Variables

Independent variable will be the web-based education video for the intervention group and a talk about diabetes educations for the control group

Intention to treat (ITT) method will be used for statistical analysis. Statistical analysis will be done using IBM SPSS Statistics version 27. Descriptive analysis will be conducted to check the error and distribution of data. Histogram with normal curve will be used for normality checking. Independent-t test will be used to investigate the difference of diabetes knowledge test between group. Paired t test will be used pretest and post-test after 6 months. Generalized Estimating Equation (GEE) will be used to investigate the effectiveness of diabetes knowledge and clinical outcome, adjusted with covariates. P<0.05 will be considered statistically significant.

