## Sample Size

Sample size was calculated based on two mean groups formula (20) , mean±sd of knowledge differences for intervention group and control group were 0.7±2.21 and -0.30±2.33 (16), 80% of power, 5% of risk error, 30% attrition rate, the sample size needed per group is 116 (total is 232).

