## Recruitment and randomisation

The study design that will be used in this study is a Blocked Randomized Control Trial (RCT) ratio one to one.

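### With 30% attrition planned, the 6-month t-tests use completers only and the GEE needs a restrictive dropout assumption; a mixed model or imputation by arm would make better use of scores already collected

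*Protocol*

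**What the plan says.** The methods are in the Protocol's own Statistical Analysis Plan section (3.12, under Independent Variables). It states the principle, "Intention to treat (ITT) method will be used for statistical analysis", and then names three methods:

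- For the comparison between arms: "Independent-t test will be used to investigate the difference of diabetes knowledge test between group". The visit is not given, nor whether the test is on scores or on changes.
- Within arms: "Paired t test will be used pretest and post-test after 6 months".
- A covariate-adjusted GEE for knowledge and the clinical outcomes. No working correlation or weighting is given.

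None of the three is named as primary.

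Section 3.6 (Sample Size) gives "mean±sd of knowledge differences for intervention group and control group were 0.7±2.21 and -0.30±2.33" and continues "80% of power, 5% of risk error, 30% attrition rate, the sample size needed per group is 116 (total is 232".

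Sections 2.2 and 3.20 put the knowledge questionnaire at baseline, 3 months and 6 months. The clinical profile is taken at baseline and 6 months only. Section 3.5 allows withdrawal at any time. Section 3.9 requires the intervention arm to watch every video and has a research assistant phone every four weeks about progress.

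**The concern.** The plan expects to lose almost a third of the outcome data, yet the methods it names are weak at handling that loss. A t-test cannot use a person who lacks the score being tested. A GEE without weights uses the visits that were observed, but in general its estimates can be trusted only if loss is completely at random or depends only on covariates in the model. Meanwhile the 3-month knowledge score, which is collected from many of those who later drop out, is information that a t-test on 6-month scores ignores.

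The two arms are also asked to do different things. If participants with low scores leave the video arm more readily than the control arm, those who remain in the video arm look better than the arm as randomised. The videos could then appear to work when they do not. The reverse pattern would hide a real effect.

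**Working it through.** **1. The plan's own figure.** The inputs from section 3.6 are a difference of 0.7 − (−0.30) = 1.0, SDs of 2.21 and 2.33, 80% power and 5% error. Two-sided testing is assumed, because it reproduces the figure.

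- Pooled variance = (2.21² + 2.33²)/2 = (4.8841 + 5.4289)/2 = 5.1565, so SD = 2.271.
- n = 2 × (1.960 + 0.842)² × 5.1565 / 1.0² = 80.9, so 81 per group.
- 81/0.70 = 115.7, so 116 per group. This matches the Protocol.

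The 80% power therefore rests on about 232 × 0.7 = 162 participants with an outcome, and 232 × 0.3 = 70 are expected to lack one.

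**2. Who enters each analysis of knowledge.**

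| Method | A participant lost after 3 months |
|---|---|
| Independent t-test at 6 months | Excluded |
| Paired t-test, baseline to 6 months | Excluded |
| GEE on three visits | Kept through baseline and 3-month scores |

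For the clinical outcomes, such a participant gives the GEE a baseline value and nothing after randomisation.

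**3. When the completer difference is biased.** Let d be the proportion lost in an arm, and g the completers' mean minus the dropouts' mean in that arm. The completer mean exceeds the mean of the whole arm by d × g. The bias in the difference (video minus control) is d₁g₁ − d₀g₀. The gaps below are assumptions, because the Protocol gives none.

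- Loss of 30% in each arm, gap in the video arm only: 0.3 × 0.5 = 0.15; 0.3 × 1.0 = 0.30; 0.3 × 2.0 = 0.60 points.
- Loss of 30% in each arm, same gap in both: 0.
- Loss of 40% against 20%, same gap of 1 or 2 points in both: 0.2 × 1 = 0.2; 0.2 × 2 = 0.4 points.

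The planned effect is 1.0 point.

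**4. Simulation with no true effect.** The setting has 116 per arm, score SD 2.27, correlation 0.5 between visits and about 31% loss at 6 months. Dropout in the video arm rises as the 3-month score falls (log-odds 1.2 per SD); control dropout is unrelated to score. At correlation 0.5 the SD of change equals the SD of the score, since √(2 × (1 − 0.5)) = 1, so this agrees with section 3.6. The correlation and the dropout mechanism are assumed.

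| Analysis | Bias (points) | Type I error |
|---|---|---|
| t-test on 6-month score | +0.33 | 15% |
| GEE, independence working correlation | +0.33 | 15% |
| GEE, exchangeable, data truly exchangeable | 0.00 | 5.0% |
| GEE, exchangeable, true correlation decaying (0.5/0.25) | +0.04 | 6.0% |
| t-test on change, equal correlations | 0.00 | 4.7% |
| Likelihood estimate using baseline and 3-month scores | 0.00 | not computed |

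Repeated runs of 2,000 to 3,000 trials put the first row at +0.33 to +0.35 and 15% to 16%. A hand check agrees: the standard error is 2.27 × √(2/81) = 0.357, and 0.33/0.357 = 0.92. The rejection rate is then P(Z > 1.96 − 0.92) + P(Z < −1.96 − 0.92) = 0.15. The change-score t-test ranged from 0 to +0.17 under other assumed correlations. With the same mechanism in both arms, the 6-month t-test had bias of about 0.01 and type I error of 4.8%.

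**5. Large-sample check with a true effect of 1.0.** This used 20,000 participants, correlation 0.55 and 30% loss per arm, tied to knowledge in the video arm only except in the first row.

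| Loss depends on | Full-data change | t-test, 6-month score | GEE, independence | GEE, exchangeable |
|---|---|---|---|---|
| Nothing | 1.007 | 1.035 | 1.031 | 1.024 |
| Observed 3-month score | 0.953 | 1.358 | 1.310 | 0.956 |
| Unseen 6-month score | 1.002 | 1.701 | 1.707 | 1.433 |

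With an independence working correlation and group-by-visit terms, the GEE reproduces the available-case means. A suitable working correlation removes most of the bias when loss depends on observed scores, but not when it depends on unseen ones.

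**The case against.** Three stronger readings are tempting, and the Protocol does not support them.

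- *No named method includes everyone randomised, so the result rests on completers.* This fits the 6-month t-tests only. The GEE keeps anyone with at least one observed visit, and in the large-sample check it kept every randomised participant.
- *The intention-to-treat statement is contradicted.* Analysing the observed data by allocated arm is compatible with that principle, and missing outcomes do not make the label false. Inflating 81 to 116 for attrition is ordinary practice and does not declare a completer analysis.
- *The result is biased whenever dropout relates to knowledge.* It is not. With equal loss and an equal gap in both arms, the bias cancels.

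The rest of the opposing case has weight. The one-arm mechanism is an assumption with no source in the Protocol. Regular phone contact could improve retention in the video arm, and section 3.9 words the four-weekly reminder about appointments for participants generally. Section 3.6 sizes the trial on differences in knowledge, so the t-test may be meant for change scores, where the illustrated bias is smaller or nil. Working correlation, imputation and sensitivity analyses are commonly left to a separate analysis plan, which may exist, so their absence is not an error in itself. If loss depends on unseen scores, a mixed model is not protected either.

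What survives concerns the methods the Protocol itself fixes. Tests on 6-month scores omit the expected 30%. The GEE's validity depends on a working correlation left open and on a missing-data assumption stricter than the collected data require.

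**Conclusion.** The point stands as an improvement to the choice of analysis. With about 70 of 232 participants expected to lack a 6-month score, the 6-month t-tests are completer analyses. The unweighted GEE is in general valid only for loss that is completely at random or depends only on covariates. A method that uses the observed baseline and 3-month scores needs the weaker assumption of missing at random.

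The size depends on how loss differs between arms. Under the assumed one-arm mechanism tied to the 3-month score, with no true effect and 31% loss, the 6-month-score t-test is off by about +0.33 points (a third of the planned 1.0), with type I error of about 15%. With a shared mechanism it is about zero. These figures illustrate what could happen and do not predict it. They apply to the 6-month-score t-test and the independence GEE, not to every method named. The sample size of 116 per group is not in question.

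**What to change.** In section 3.12:

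- Name one primary analysis: a linear mixed model for repeated measures on knowledge at baseline, 3 and 6 months, with group-by-visit terms and unstructured covariance, including all randomised participants as allocated. Alternatively, multiply impute missing 6-month scores separately by arm from the baseline and 3-month scores, then fit the GEE.
- State that this rests on data missing at random, and say what intention to treat means for participants without a 6-month score.
- Label the independent and paired t-tests as supportive completer analyses.
- Add one missing-not-at-random (delta) sensitivity analysis. For example, lower the imputed video-arm scores by 0.5, 1.0 and 2.0 points; at 30% loss this shifts the estimated effect by 0.15, 0.30 and 0.60.

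The cost is revised wording and a little more analysis work. It needs no new data, no extra visit and no change to the sample size.

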## Specific objective

1. To develop web-based education videos for type 2 diabetes patients in primary care.
2. To identify the sociodemographic characteristics (age, gender, ethnicity, education level, marital status, employment status, income, smoking status, history of hospitalisation due to complication of type 2 diabetes) of the type 2 diabetes patient in the primary care clinic among intervention and control groups at baseline.
3. To determine the knowledge scores and clinical outcome (HbA1c, blood pressure, fasting lipid profile, BMI, waist circumference) among intervention and control groups at baseline.
4. To investigate the effectiveness of web-based education videos and compare on the knowledge, diabetes empowerment and clinical outcome (HbA1c, blood pressure, fasting lipid profile, BMI, waist circumference) at baseline, 3months and 6 months between and within the intervention and control groups.

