# Methodology

## Study Type and Design

The study design that will be used in this study is a Blocked Randomized Control Trial (RCT) ratio one to one. The samples will be from Klinik Kesihatan Cheras Baru. The study will be conducted and evaluated by the requirement in the Consolidated Standards of Reporting Trials (CONSORT) Statement. (19)

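### Knowledge is compared between groups by an unadjusted t-test and by a GEE with unnamed covariates, with neither designated as deciding; one baseline-adjusted primary analysis would cost nothing and be at least as powerful.

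*Protocol*

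**What the plan says.** Section 3.12 (Statistical Analysis Plan) describes two between-group analyses of knowledge, which it names as the primary outcome:

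- "Independent-t test will be used to investigate the difference of diabetes knowledge test between group". It gives no time point, no baseline term, and no statement of raw or change score.
- "Generalized Estimating Equation (GEE) will be used to investigate the effectiveness of diabetes knowledge and clinical outcome, adjusted with covariates". The covariates are not listed, and the text does not say whether baseline knowledge is a covariate, a repeated response, or absent.

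A paired t-test for the 6-month pre/post comparison is planned as well. A single significance threshold, P<0.05, applies throughout, and no analysis is called primary.

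Section 3.6 (Sample Size) sizes the trial on within-person change: "mean±sd of knowledge differences for intervention group and control group were 0.7±2.21 and -0.30±2.33", with 80% power, "5% of risk error" and "30% attrition rate", giving 116 per group. Knowledge is to be compared "at baseline, 3months and 6 months between and within the intervention and control groups" (section 2.2), and the schedule in section 3.20 has the questionnaire at all three visits.

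**The concern.** The sizing rests on the spread of change scores. The t-test sentence mentions neither change nor baseline. If the test is applied to raw follow-up scores, its standard deviation is not the one used for sizing, and the 80% in section 3.6 need not describe it. A chance difference in baseline knowledge between the arms would also pass into that comparison uncorrected.

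Two further things are at stake. First, an unadjusted test of either kind gives up precision that the baseline questionnaire already supplies. Second, two analyses of the same hypothesis at the same threshold, with no order between them, leave room to lean on whichever gives the smaller P value.

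**Working it through.** **Inputs from the protocol.** Mean change 0.7 (SD 2.21) and -0.30 (SD 2.33), 80% power, 5% error and 30% attrition (section 3.6); 1:1 allocation (section 3.1).

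**Assumptions, not in the protocol.** Two-sided test (this reproduces the stated size; one-sided gives 64 completers and 92 per arm). Equal variance of the knowledge score at baseline and follow-up. A baseline/follow-up correlation ρ, shown from 0.2 to 0.8.

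**Step 1: reproduce the stated size.**
- Difference = 0.7 - (-0.30) = 1.0.
- Average change variance = (2.21² + 2.33²)/2 = 5.157, so SD = 2.27.
- n = 2 × 5.157 × (1.960 + 0.842)² / 1.0² = 80.9, rounded up to 81 per arm.
- 81/0.70 = 115.7, rounded up to 116 per arm.

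This matches exactly.

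**Step 2: variance under each analysis.** With equal variance σ² at both times, change variance = 2σ²(1-ρ). Hence:
- change score: 5.157 at every ρ;
- raw follow-up score: σ² = 5.157/[2(1-ρ)];
- baseline-adjusted: σ²(1-ρ²) = 5.157 × (1+ρ)/2.

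The raw variance equals the change variance only at ρ = 0.5. The adjusted variance never exceeds either of the others, because (1+ρ)/2 ≤ 1 and 1-ρ² ≤ 1.

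**Step 3: power with 81 completers per arm.** Noncentral t with 160 degrees of freedom and noncentrality 1.0/√(2V/81), where V is the variance from step 2. For example, at ρ = 0.6:
- raw: V = 5.157/0.8 = 6.446, noncentrality 2.51, power 70%;
- adjusted: V = 5.157 × 0.8 = 4.125, noncentrality 3.13, power 88%.

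| ρ | Change-score t-test | Raw-score t-test | Baseline-adjusted |
|---|---|---|---|
| 0.2 | 80% | 94% | 95% |
| 0.4 | 80% | 86% | 91.5% |
| 0.5 | 80% | 80% | 90% |
| 0.6 | 80% | 70% | 88% |
| 0.7 | 80% | 58% | 86% |
| 0.8 | 80% | 42% | 84% |

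The 80% is 79.6% by noncentral t and 80.0% by the normal approximation. The 91.5% becomes 92% by the normal approximation.

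**Step 4: the two undesignated analyses.** Suppose success could be declared on either an unadjusted t-test or a baseline-adjusted analysis. In 20,000 simulated null trials with 81 per arm, using ANCOVA in place of an adjusted GEE, the false-positive rate was about 7% to 8% at correlations of 0.5 to 0.7, instead of 5%. The protocol does not say that either would suffice; it simply does not exclude it.

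**The case against.** A reader might infer that the trial is underpowered, or that its only between-group test is an unadjusted t-test. The protocol supports neither inference.

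- **The t-test may be on change scores.** The word *difference* in section 3.12 can mean the same knowledge differences used in section 3.6. On that reading the test matches the sizing and the 80% is delivered. This stands.
- **The direction is conditional.** Below a correlation of 0.5 the raw-score test has more than 80% power. The only psychometric figure given is Cronbach's alpha of 0.573 (section 3.10). It is not a test-retest correlation, but it makes a very high correlation less likely, so 42% is an end-of-range case. This stands too.
- **The GEE may be the intended efficacy analysis.** Its sentence speaks of effectiveness, as do the objectives, and its covariates may include baseline knowledge. The t-test has no time point and might even serve the baseline comparison in specific objective 3. Loss of precision, and exposure to baseline imbalance, follow only if the t-test decides or the GEE leaves baseline out. This stands as a limit on the claim.
- **A separate SAP may settle these details.** That is possible, and a missing covariate list alone would not be a finding. But section 3.12 commits to specific tests, including an unadjusted between-group test of the primary outcome beside a second analysis at the same threshold. The point concerns what is fixed there.

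None of this touches the recommendation, which improves on both readings of the t-test.

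**Conclusion.** The point holds as a free improvement and a clarification, not as a demonstrated power deficit. Section 3.12 sets an unadjusted t-test beside a GEE with unspecified covariates for the same outcome and designates neither, while baseline knowledge is available on everyone.

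The gain over a change-score t-test is 4 to 15 percentage points of power (84% to 95% against 80%). Over a raw-score t-test it ranges from about 1 point at a correlation of 0.2 to 42 points at 0.8. A raw-score test falls below the stated 80% only when the correlation exceeds 0.5.

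These figures rest on 81 completers per arm, a difference of 1.0, a change SD of 2.27, equal variances at both times, and a correlation the protocol does not give. The sample size is correctly calculated on its own terms and needs no change.

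**What to change.** In section 3.12, name one primary analysis of knowledge that adjusts for baseline knowledge. Either of these will do:

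- ANCOVA at one named follow-up visit (for example 6 months), with group and baseline score as terms; or
- the planned GEE with only the 3- and 6-month scores as responses, and group, visit, group-by-visit and baseline score as terms, stating which visit's group contrast decides. Limiting the responses to post-baseline visits keeps baseline from entering the model twice.

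Make the independent t-test descriptive. Adjust each clinical outcome for its own baseline; section 3.20 schedules these at baseline and 6 months only, so this is an adjusted comparison at 6 months. Keep 116 per arm.

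The cost is a few lines of wording. No added data or participants are needed, and the analyses can be run in the planned software.
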